### Screening of potential participants for cervicogenic dizziness

A three step process will be followed to identify people with cervicogenic dizziness. Firstly, an initial phone screening will be conducted by a physiotherapist. Secondly, if potential participants are still thought to have cervicogenic dizziness after the phone discussion they will then be examined physically by the physiotherapist. Thirdly, if not excluded by the physiotherapist at that stage they will have a clinical examination by a neurologist including peripheral vestibular function testing.

#### Phone screening

During the phone screening a history will be taken by the physiotherapist to establish that the person does have dizziness described as imbalance or unsteadiness. If the person has any other types of dizziness such as vertigo, migrainous vertigo, pre-syncope, signs and symptoms of vertebral artery ischaemia (dysarthria, drop attacks, facial paraesthesia, syncope), orthostatic hypotension or psychogenic dizziness 
[33] they will be excluded. If the dizziness is described as imbalance or unsteadiness it must be established that the imbalance is not due to another cause including musculoskeletal problems, neuromuscular problems, and conditions affecting the brain such as Parkinson’s disease, stroke, cerebellar ataxia, multiple sclerosis, Vitamin B12 deficiency or alcoholism. Then it must be established that there is a related history of neck pain and or/stiffness. The unsteadiness or poor balance must also be exacerbated by cervical spine movements or positions to be considered to be due to cervicogenic dizziness.

#### Physical assessment by a physiotherapist

Those who have passed through the phone screening and are thought to have cervicogenic dizziness then undergo a physical assessment by a physiotherapist. This physical examination includes:

– The Dix-Hallpike manoeuvre performed to determine whether the person has dysfunction of the semi-circular canals 
[34]. In this test, the participant sits on the examination table while the clinician rotates the participant’s head to 45 degrees then quickly lays the participant straight back so that their head is extended below the horizontal. The production of nystagmus indicates benign paroxysmal positional vertigo.

– Blood pressure measured in sitting and immediately after rising to standing with a digital sphygmomanometer. A normal blood pressure response to positional change will indicate that neurocardiogenic syncope is an unlikely cause of the dizziness 
[33]. A drop in systolic blood pressure of > 30mm Hg or a drop of 10mm Hg in diastolic blood pressure is indicative of orthostatic hypotension 
[33].

– Smooth visual pursuit movements assessed by the ability to track a slowly moving object. The examiner looks for asymmetry of eye movement which may indicate a cerebellar lesion 
[33].

– The vestibulo-ocular reflex with the participant sitting maintaining a gaze on a stationary target and performing small oscillations of the head side-to-side and up-and-down. Abnormal responses such as an inability to maintain the gaze for 60 seconds due to dizziness, blurry vision or double vision may indicate peripheral or central nervous system dysfunction 
[33].

– Cervical range of motion assessment to determine whether the participant has a restriction of movement which may indicate cervical spine dysfunction consistent with cervicogenic dizziness 
[5]. The participant is asked to move their neck into flexion, extension, left rotation, right rotation, left lateral flexion and right lateral flexion and report any symptoms such as dizziness or pain.

– Palpation of the upper cervical spine (occiput to C3) performed to identify any stiff and/or painful joints which may indicate dysfunction in the upper cervical spine 
[5].

– Decreased balance has been reported in people with cervicogenic dizziness 
[6]. To assess balance, participants will be asked to hold tandem stance for 30 seconds. Tandem stance is a clinical measure of standing balance considered to assess postural steadiness in a heel-to-toe position 
[34].

#### Examination by a neurologist

If the participant is not excluded after this preliminary screening, they are further assessed by a neurologist to exclude central nervous system, vestibular and other non-cervical causes of the dizziness. This examination will include tests for vestibulo-spinal function, the vestibulo-ocular system, disequilibrium such as gait and balance testing, a repeat of the Dix-Hallpike manoeuvre and peripheral vestibular function testing.

### Randomisation

Participants who were not excluded during the screening process will be randomly allocated to one of three intervention groups: placebo, Mulligan SNAGS and Maitland mobilisations. An independent statistician will produce a computer generated randomisation sequence which will be placed in sequentially numbered opaque sealed envelopes. The randomisation sequence will contain equal numbers of participants in each group.

### Interventions

A physiotherapist with post graduate qualifications and a minimum of 20 years experience in the field of manual therapy will perform all the interventions during the study to all the participants.

#### Placebo

One group of participants will have a placebo intervention consisting of infrared therapy laser which has been deactivated by the manufacturer. A medical laser is commonly used by physiotherapists to treat musculoskeletal symptoms 
[35]. To the participant, the placebo laser device (a Therapower 40mW laser, serial No 020601, Meyer Medical Electronics, Mordialloc, Australia) will appear to operate normally with a light flashing and a beeping sound, but it will not produce any effective emission. The deactivated laser, which has been shown to have a very strong placebo effect 
[4,35], will be applied for two minutes to each of three sites on the neck, with the pen at a distance of 0.5-1 cm from the skin 
[35].

#### Mulligan SNAGs

Another group of participants will receive SNAGs as described by Mulligan 
[36]. The participant, in the sitting position, is asked to move their head in the direction that particularly produces their symptoms. As the participant moves their head, the physiotherapist gently glides the C1 or C2 vertebra anteriorly and sustains the glide through the movement. During the application of the glide, the participant should stay symptom-free and is instructed to stop moving if any dizziness is produced. This movement is repeated six times at the first treatment session as recommended by Mulligan. At the subsequent treatment sessions provided no dizziness is experienced the SNAG is performed ten times and gentle over pressure can be applied. A second SNAG in another implicated direction of movement may be added to treatment. After the second treatment the participant will be advised to do a self-SNAG (six repetitions) as a home exercise once daily. Written and pictorial instructions for the home exercise will be provided. A second home treatment self-SNAG may be added for another implicated movement direction after the third treatment. The participant will be asked to perform the home exercises once daily for 12 months.

#### Maitland mobilisations

The physiotherapist will palpate the neck to find the three most dysfunctional joints and then perform passive joint mobilisations to those joints (as described by Maitland et al.) 
[32]. A passive joint mobilisation is where the therapist uses their thumbs to rhythmically apply pressure to a vertebra usually in a posterior to anterior direction. It is usually applied three times for 30 seconds to dysfunctional joints or determined by the clinical judgement of the physiotherapist 
[32]. After the second treatment the participant will be advised to perform range of motion exercises into flexion, extension, right rotation, left rotation, left lateral flexion and right lateral flexion, three times in each direction, once a day for 12 months. Written and pictorial instructions for the exercises will be provided.

### Outcome measures

Socio-demographic data will be collected at baseline including the participant’s age, gender, and time since commencement of dizziness. The primary and secondary outcomes will be measured at baseline, after the last treatment, at six weeks, 12 weeks, six months (questionnaires only), and one year after treatment is completed. All follow-up assessments will be conducted by researchers blinded to the participants’ group allocation. The researchers conducting the data entry process will be blinded to group allocation.

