**Methods:**

Participants with symptoms of dizziness described as imbalance, together with a painful and/or stiff neck will be recruited via media releases, advertisements and mail-outs to medical practitioners in the Hunter region of NSW, Australia. Potential participants will be screened by a physiotherapist and a neurologist to rule out other causes of their dizziness. Once diagnosed with cervciogenic dizziness, 90 participants will be randomly allocated to one of three groups: Maitland mobilisations plus range-of-motion exercises, Mulligan SNAGs plus self-SNAG exercises or placebo. Participants will receive two to six treatments over six weeks. The trial will have unblinded treatment but blinded outcome assessments. Assessments will occur at baseline, post-treatment, six weeks, 12 weeks, six months and 12 months post treatment. The primary outcome will be intensity of dizziness. Other outcome measures will be frequency of dizziness, disability, intensity of cervical pain, cervical range of motion, balance, head repositioning, adverse effects and treatment satisfaction. Economic outcomes will also be collected.

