## Methods/Design

A prospective RCT with unblinded treatment and blinded outcome assessment will be conducted in the School of Health Sciences at the University of Newcastle, Australia. Participants (with cervicogenic dizziness) will be randomly allocated to SNAGs, Maitland passive joint mobilisation or placebo groups. Each participant will receive two to six treatments by an experienced physiotherapist over six weeks at the discretion of the treating therapist who will use their clinical judgement to determine the specific dosage based on the participant’s response. Treatment will cease if the participant perceives the condition is adequately improved or if the improvement plateaus, that is, no further improvement is evident over three successive visits.

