#### Controlling bias

To minimise bias randomisation, concealed allocation, specific inclusion and exclusion criteria, blinded outcome assessment, patient blinding, blind data analysis, and intention to treat analysis have been used. It was not possible to blind the physiotherapist performing the interventions.

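### Every post-baseline assessment is timed from a treatment end date that depends on response, so participants, and possibly arms, are assessed at unequal times since randomisation

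*Protocol article*

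**What the plan says.** The Abstract (Methods) and the Outcome measures section agree on the anchor. The Abstract has "Assessments will occur at baseline, post-treatment, six weeks, 12 weeks, six months and 12 months post treatment". Outcome measures places one assessment straight after the last session and the others "at six weeks, 12 weeks, six months (questionnaires only), and one year after treatment is completed". Nothing in the text shown schedules a visit from randomisation; the flow chart (Figure 1) is not reproduced and could not be checked.

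Methods/Design makes the end of treatment variable: "Each participant will receive two to six treatments by an experienced physiotherapist over six weeks at the discretion of the treating therapist". It adds that "Treatment will cease if the participant perceives the condition is adequately improved or if the improvement plateaus", and it defines a plateau as a run in which "no further improvement is evident over three successive visits". The Interventions section has one physiotherapist treating everyone in all three groups. Of that person, Controlling bias says "It was not possible to blind the physiotherapist performing the interventions".

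Outcome assessors are blinded, and Controlling bias lists patient blinding and intention-to-treat analysis. The primary outcome is a 100 mm VAS of average dizziness over the previous week. Statistical methods analyses outcomes with a mixed model containing time, group and their interaction, and also compares groups by t-test at each time point.

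**The concern.** Randomisation makes the arms comparable at equal times since randomisation. Here the clock for every follow-up visit starts at an event that happens after randomisation and is partly driven by symptoms. Two things could follow.

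First, if one arm tends to stop earlier, visits with the same label fall at different elapsed times in the two arms, and any natural change over time enters the comparison. Different stopping by arm is plausible: response is what the trial tests, and the therapist knows the allocation.

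Second, when treatment stops because a participant feels better, and the assessment follows at once with a one-week recall, a chance good week can be both the reason for stopping and the recorded outcome.

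Blinded assessors do not remove either effect, because the visit date is already set before they see the participant. Intention-to-treat keeps participants in their arms but does not equalise assessment times.

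**Working it through.** **Plan's own figure.** The protocol gives no number for timing. Its DHI sample size (difference 11, SD 15, two-sided 5%, 80% power) reproduces: 2 × (1.960 + 0.842)² × 15² / 11² = 29.2, so 30 per group. Nothing below changes it.

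**Elapsed time.** Inputs: two to six sessions within six weeks (Methods/Design); visits at 0, 6, 12, 26 and 52 weeks after the last session (Outcome measures). Assumption: sessions are weekly, with session k in week k after randomisation. Visit week = k + offset.

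| Visit | 2 sessions | 6 sessions |
|---|---|---|
| Post-treatment | 2 | 6 |
| Six weeks | 8 | 12 |
| 12 weeks | 14 | 18 |
| Six months | 28 | 32 |
| One year | 54 | 58 |

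The spread between individuals is 6 − 2 = 4 weeks at every visit. That is a threefold ratio at the first visit (6/2) and about 7% at one year (4/58 = 6.9%; 4/54 = 7.4%).

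**Who stops early.** A plateau needs three successive visits, so it cannot be shown after two sessions. Under the stated rules, a stop at two points to perceived improvement. Later stops can reflect improvement or lack of it.

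**Selection at the post-treatment visit.** Simulation with no true change in anyone.

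- From the protocol: SD 24 mm (2.4 on the 0–10 scale in Sample size calculation); target difference 20 mm (2 units).
- Assumed: weekly visits; stop at the first of visits 2 to 5 with improvement of at least 10, 20 or 30 mm from baseline, otherwise at visit 6; constant between-week correlation of 0.5, 0.7 or 0.8. The plateau rule is not modelled.

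Mean apparent improvement, compared with 0 at a fixed week-6 visit, when the score that triggers stopping is itself the recorded outcome:

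| Threshold | r = 0.5 | r = 0.7 | r = 0.8 |
|---|---|---|---|
| 10 mm | 10.1 mm | 7.6 mm | 6.0 mm |
| 20 mm | 8.8 mm | 5.8 mm | 3.7 mm |
| 30 mm | 6.4 mm | 3.2 mm | 1.4 mm |

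Sensitivity to the gap between stopping and assessment: if the following week's score is recorded instead, the shift is 0.0 mm under constant correlation. If correlation decays with time (first-order autoregressive, 0.5 or 0.7 per week, 20 mm threshold), it is about 4.1 or 3.4 mm. Six weeks after stopping, the shift is 0 under constant correlation and below 1 mm under the decaying form.

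**Between arms.** If both arms stop by the same rule with no true effect, the shift cancels. With a 20 mm threshold in one arm and 30 mm in the other, the spurious difference is about 2.5 mm (8.8 − 6.4 = 2.4; 5.8 − 3.2 = 2.6; 3.7 − 1.4 = 2.3). In the extreme case where only one arm ever stops early, the standard error of a difference at 30 per group is 24 × √(2/30) = 6.2 mm. The false-positive rate of the post-treatment t-test then runs from about 6% (shift 1.4 mm) to about 37% (shift 10.1 mm), instead of 5%.

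**The case against.** The case against is substantial, and most of it limits the size of the point.

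- A reader might infer that the arms are assessed at different times. The protocol does not show that. One rule and one therapist apply to all three groups, and arms diverge only if stopping diverges.
- A reader might infer that the unblinded therapist alone decides when improvement is adequate. Methods/Design makes that trigger the participant's own perception, and patients are listed as blinded. Therapist discretion over the number of sessions remains.
- A reader might set a 6 to 9 mm shift (20 mm threshold, correlation 0.7 or 0.5) against the 20 mm target and call it a bias of 29% to 44%. That is a shift within one arm. It becomes a between-arm bias of that size only if the comparator never stops early, and it needs the triggering score to be the recorded one. The protocol states no interval between last session and assessment.
- The selection effect does not carry through to one year, which is the horizon the Study aims stress.
- The direction of the elapsed-time effect is unclear. A better arm that stops earlier is also assessed earlier, with less time for natural recovery, which works against it. Symptoms must already have lasted more than three months, and no recovery rate is given.
- It is tempting to add that cost diaries cover unequal periods. The protocol gives no start or end date for the diary, so this is unsupported.
- Timing from the end of treatment answers a legitimate question, namely how long benefit lasts once treatment stops.

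All of these stand. None alters the fact that the schedule ties assessment dates to a response-dependent event, or gives a reason to expect equal stopping across arms.

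**Conclusion.** The point holds as a design weakness with a cheap remedy, not as a demonstrated bias. Assessment dates depend on a post-randomisation, response-driven event. On the assumption of weekly sessions, individuals can be up to about 4 weeks apart in time since randomisation: a large share of elapsed time at the post-treatment and six-week visits, about 7% at one year. Arms may differ if stopping differs by arm; the sign of any resulting bias cannot be fixed from the protocol. The favourable-moment effect concerns essentially the post-treatment visit. Its within-arm size is roughly 0 to 10 mm, depending on the assumed correlation, stopping threshold and gap before assessment. The later comparisons, including one year, are little affected.

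**What to change.** Leave the treatment rules as they are and change only the assessment clock. Schedule all assessments at fixed times from randomisation, with the first at the end of the six-week treatment window for everyone. Keeping the present intervals would put the visits at weeks 6, 12, 18, 32 and 58 (6 + 0, 6, 12, 26 and 52).

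If the visits cannot be moved, the minimum is to record each assessment's actual time since randomisation and use it in the mixed model. This deals with unequal elapsed time but not with selection at the post-treatment visit, where the date itself depends on symptoms.

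In either case, report the number of sessions and the date of the last session by arm, so that readers can see whether stopping differed.

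The cost is visit-schedule wording and booking rules; the sample size stays at 30 per group. The downside is that early finishers would have a few weeks between their last session and their first assessment, so that visit no longer measures the state immediately after treatment for them.

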#### Primary outcome

Severity of dizziness (an average level over the previous week) will be measured with a 100 mm horizontal visual analogue scale (VAS). The VAS has been used successfully to measure dizziness in other studies 
[4,37-39].

#### Secondary outcomes

1) Frequency of dizziness will be measured on a six-point rating scale (0 = no dizziness, 1 = dizziness less than once per month, 2 = 1–4 episodes of dizziness per month, 3 = 1–4 episodes of dizziness per week, 4 = dizziness once daily, 5 = dizziness more than once a day or constant). This scoring method has been used by several researchers 
[4,8,37,38] to measure frequency of dizziness.

2) Disability caused by dizziness will be measured with the Dizziness Handicap Inventory (DHI). This is a health status measure specifically designed to assess dizziness. The DHI assesses the quality of life using three subscales evaluating the impact of dizziness on the functional, emotional and physical aspects of everyday life 
[40]. The highest possible score is 100, indicating maximum self-perceived handicap. The DHI has been shown to be a highly reliable and responsive tool 
[40-42].

3) Severity of neck pain (an average level over the previous week) will be assessed with a 100 mm VAS. There is much evidence supporting the high validity of the VAS for measuring pain intensity 
[43-47].

4) Global perceived effect will be used to assess satisfaction with treatment and measured by self-assessment on a six-point scale (0 = no benefit, 1 = minimal benefit, 2 = some benefit, 3 = a lot of benefit, 4 = great benefit, 5 = maximal benefit) as used in other studies 
[4,48,49].

5) Posturography will be used to identify and quantify disturbances in balance. Body sway will be measured with a Chattecx Balance Dynamic System (Serial No 1001, Chattecx Corporation, the Chattanooga Group, Tennessee). Recordings will be performed during the following tasks.

· standing erect with the neck in the neutral position with eyes open

· standing erect with the neck in the neutral position with eyes closed

· standing erect with the neck extended

· standing erect with the neck in left rotation

· standing erect with the neck in right rotation

· standing on a moving platform.

Posturography has been used in many studies to assess people with dizziness and has been found to have good correlations with the participant’s symptoms 
[4,6,8,37].

6) A Cervical Range of Motion (CROM) goniometer (Performance Attainment Associates, [name]), which has been shown to be a reliable tool with good validity 
[50], will be used to measure cervical spine movements. Active flexion, extension, left and right rotation, and left and right lateral flexion will be measured. Each movement will be measured three times and the average taken.

7) Neck repositioning sense will be assessed with the CROM device. This task tests the participant’s ability to accurately reposition their head and neck. The participant is first seated with their head in a neutral position. They are then asked to close their eyes and to move their head into rotation. At mid-range of rotation, the participant will be asked to stop, hold their head steady and think about their position. This position is referred to as the ‘target position’. After 5 seconds, the participant returns to the starting position and then attempts to find the target position again at which point a reading is taken. The number of degrees difference between the target position and the attempt to find it are calculated. This is performed three times for both right and left rotation and the average taken for each direction of rotation movement.

Information about adverse events will be collected by the treating physiotherapist at each treatment session and by the research assistant at each follow-up measurement session using open-ended questions as per normal clinical practice.

Participants will be given a diary and asked to log medication use, visits to a medical practitioner, visits to other health professionals, time off work, changes in social engagements and adherence to home exercises.

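### The printed dizziness-frequency grades leave 5–6 episodes a week without a grade and can overlap at about once a week

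*Protocol article*

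**What the plan says.** In the Protocol article, Secondary outcomes, item 1, frequency of dizziness is a six-point rating. The lowest two grades are "0 = no dizziness, 1 = dizziness less than once per month", the middle three are "2 = 1–4 episodes of dizziness per month, 3 = 1–4 episodes of dizziness per week, 4 = dizziness once daily", and the top grade is "5 = dizziness more than once a day or constant". No rule is printed for a frequency that falls between two grades or fits two of them.

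Of the scale's origin, the article says: "This scoring method has been used by several researchers".

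Under Outcome measures, the primary and secondary outcomes are "measured at baseline, after the last treatment, at six weeks, 12 weeks, six months (questionnaires only), and one year after treatment is completed". Under Statistical methods, the outcomes enter generalized linear mixed models and are also compared between groups at each time point with t-tests.

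**The concern.** A rating scale should give every possible answer one grade and only one. Here the unit changes from month to week to day as the grades rise, and the limits do not meet where the unit changes.

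The upper break matters because moving from daily dizziness to a few episodes a week is a plausible course of improvement, and it passes through a range that the scale cannot record. A participant in that range has to be put in grade 3 or grade 4, and nothing printed makes the choice the same at the next visit. The lower break, at about once a week, allows the same thing between grades 2 and 3. Either way a one-grade change can be recorded when nothing has changed, or a real change can be hidden.

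The diary contents listed in the article do not include dizziness episodes, so nothing described there would allow the ratings to be regraded later.

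**Working it through.** The plan gives no figure to reproduce on this point. The check converts the printed grades to a common unit and looks for gaps and overlaps.

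**Inputs** (Secondary outcomes, item 1): the six grades as printed. Once daily is taken as 7 episodes a week. The article does not define the length of a month, so three lengths are used as assumptions: 28 days (28/7 = 4 weeks), the average calendar month (30.44/7 = 4.35 weeks) and 31 days (31/7 = 4.43 weeks).

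**Formula:** episodes per month = episodes per week × weeks per month. Grade 2 applies if the monthly figure lies from 1 to 4, grade 3 if the weekly figure lies from 1 to 4, grade 4 if the weekly figure is 7, and grade 5 if it is above 7.

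| Episodes per week | 28-day month | Average month | 31-day month |
|---|---|---|---|
| 0.5 | 2.0 a month: grade 2 | 2.17: grade 2 | 2.21: grade 2 |
| 1 | 4.0 a month: grades 2 and 3 | 4.35: grade 3 | 4.43: grade 3 |
| 4 | grade 3 | grade 3 | grade 3 |
| 5 | none | none | none |
| 6 | none | none | none |
| 7 | grade 4 | grade 4 | grade 4 |
| 8 | grade 5 | grade 5 | grade 5 |

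**Gap.** Both sides of the gap are stated per week or per day, so month length plays no part. Five and six a week are unassigned in every column.

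**Overlap.** As a rate, the double fit at once a week appears only with a 28-day month. Participants, however, count whole episodes. With one episode every 7 days, the number in a month depends on which day the first one falls:

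- 28 days: 4 episodes from all 7 starting days.
- 30 days: 4 episodes from 5 of the 7 starting days, 5 from the other 2.
- 31 days: 4 episodes from 4 of the 7 starting days, 5 from the other 3.

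A count of 4 is grade 2 by the month and grade 3 by the week, so the overlap is real but depends on how the month is counted.

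**Size.** Each misfit moves a rating by one grade on a 0–5 scale. The article does not say how many participants would be affected. As an illustration only, if k of the 30 in a group are misgraded in the same direction at a visit, the group mean moves by k/30 of a grade: 0.10 for k = 3 and 0.20 for k = 6 (assumed values). If the errors go both ways they partly cancel in the mean and appear as extra variance instead.

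**The case against.** The strongest reply is that this is an existing scale already used in several studies, that keeping it unchanged protects comparability, and that the harm is small. Much of that stands. Frequency is one of seven numbered secondary outcomes and being listed first gives it no stated rank; the primary outcome is the severity VAS, and the sample size rests on the DHI and a VAS. Follow-up assessors are blinded, so an arbitrary choice between neighbouring grades should fall on the groups mostly alike. It need not do so entirely, since only the participant can report how often the dizziness occurs. The overlap also disappears when an average calendar-month rate is used. But earlier use does not make the grades exhaustive, and the article does not say how earlier studies handled 5–6 episodes a week.

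A second reply is that a journal article condenses the full protocol, which might hold scoring instructions. That does not excuse the gap: all six grades are printed as the definition, so this is a stated rule that is incomplete, not a detail left out.

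A reader might also infer that the two lowest non-zero grades, being monthly, cannot be scored at the visit straight after treatment. The documents do not support this. No printed window rules out a monthly answer, and Methods/Design says "Each participant will receive two to six treatments by an experienced physiotherapist over six weeks", so treatment can last longer than a month. When treatment ends early, a one-month look-back would take in some pre-treatment time, but the article does not give the interval between sessions, and any figure for the share would be an assumption. Nor is the lack of a printed recall period for this item a fault here: it is questionnaire detail that an article commonly leaves out.

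**Conclusion.** The point holds for the grade definitions only. The gap at 5–6 episodes a week is certain from the printed text. The overlap at about once a week holds if a month is taken as four weeks or episodes are counted whole, and not for an average calendar-month rate. A stable participant can therefore be graded one step apart at different visits. The consequence is modest: noise, probably mostly unrelated to treatment group, in a secondary outcome analysed at every time point. How much noise depends on how many participants have those frequencies, which the article does not say. The primary outcome and the sample size are untouched, and nothing here is a reason to leave out the comparison at the post-treatment visit.

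**What to change.** Keep the six codes and their order, and change two definitions:

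- Grade 2: at least once a month but less than once a week.
- Grade 3: at least once a week but less than daily.

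The limits then meet. Once a week is grade 3 only, and 5 or 6 a week is grade 3. If the sponsor prefers to leave the scale's wording as it is, a scoring note with the same two rules does the same job. Whichever is chosen should apply in the same way at every visit, from baseline to one year.

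The cost is two reworded options or a one-line note. The small downside is a slight departure from the wording used in earlier studies, which should be mentioned when results are set beside them. No change to the visit schedule or to the planned comparisons is needed. In particular, a fixed 4-week recall should not be added as part of this correction: participants with no dizziness and those with it less than once a month could not then be told apart reliably.
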